## Discussion

Hospitalization can be a window of opportunity in which to engage the patient who is drinking at hazardous levels in a BI discussion, linking alcohol use to acute/chronic health problems, and then assessing and supporting personal motivation to change drinking behavior, particularly if the hospital admission is alcohol related. This preventative, public health-oriented approach is designed to help avert the physical and psychosocial consequences of hazardous alcohol consumption for individuals and their families. Based on this rationale, and on evidence of the efficacy of BI in other health-care settings, hospital accreditation and quality assurance bodies in the United States have issued and endorsed performance measures pertaining to alcohol BI for hospitalized patients.

Several features of our trial represent improvements in study design over other BI trials, particularly those with inpatients; these features are discussed in the following sections.

### Attention to potential AR

Our three-arm design allows us to compare the effect of the intervention with that of usual care in the presence or absence of extensive alcohol-related assessment. Unequal changes in the primary dependent variables (number of drinks/week, number of binge drinking episodes, change in alcohol screening status) across the two control groups will suggest the presence of AR. To further reduce potential AR, we are limiting the number, scope, and frequency of assessments [21]. We are using only one instrument each for two of the five dependent variables and are limiting the assessment of alcohol use/hazardous drinking to six items. Also, to minimize AR, we have only one assessment timepoint following baseline. Additionally, normative feedback about drinking behavior to both control group participants is provided within the context of general health maintenance recommendations [21].

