### Arm 1: Brief intervention

Arm 1 comprises the experimental BI condition (Table 3). The three-part BI is adapted from the Brief Negotiated Interview [34] and supplemented with alcohol-related patient education materials available through the VA [35,36] and NIAAA [37]. Part I, the core BI, consists of a multi-component motivational discussion with the nurse interventionist within 12 hours of baseline assessment, which includes personalized risk feedback, advice to abstain or reduce consumption, and the negotiation of an individual change plan [28,34,38,39]. Part II consists of a single, brief, in-hospital or telephone follow-up session, with the same nurse interventionist, to briefly reinforce the original intervention, discuss and “troubleshoot” the patient’s change plan, and offer additional encouragement. Part III of the intervention consists of a brief follow-up telephone call 2 weeks following hospital discharge, during which the same nurse interventionist again briefly reinforces the original intervention, discusses the patient’s change plan, and offers additional encouragement (Table 3). Typical BI follow-up periods for hospitalized patients range from one week (for written materials) to one month (for additional intervention) [12,40]. We selected a 2-week period in order to verbally reinforce recent intervention material, while allowing recently hospitalized patients time to readjust and resume self-care practices. For patients who do not initially establish an alcohol consumption goal or initiate a change plan during the initial BI, the follow-up session focuses on exploring and supporting general readiness to change.

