**Table 3 Tab3:** **Components of 3-part brief intervention for hospitalized hazardous drinkers**

**Part I: Core brief intervention (~15 minutes)** [28,34,38,39]	
●	Expression of concern about the patient’s level of alcohol consumption
●	Personalized feedback linking alcohol use and health
●	Linkage of alcohol to *admitting* diagnosis, if applicable
●	Advice to abstain/reduce alcohol consumption to below NIAAA limits
●	Assessment of motivation/readiness to change drinking behavior
●	Support for choosing an alcohol consumption goal
●	Strategies/encouragement for reaching alcohol consumption goal (change plan)
●	Potential referral to specialty care or additional support

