**Part II: In-hospital follow-up session (12–24 hours after core brief intervention, ~15 minutes)**	
●	Basic reinforcement of core brief intervention
●	Re-assessment and support of motivation and review of change plan (if applicable)
●	Discussion of challenges/barriers to change
●	Consideration of additional strategies for change plan
●	Support and encouragement for reaching goal

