### Arms 2 & 3: Control conditions

Arm 2 (AC) and Arm 3 (AC-LA) comprise the control conditions. Patients in Arms 2 and 3 receive healthy lifestyle brochures that address general healthy lifestyle behaviors such as dietary recommendations, tobacco cessation, and weight management. Brochures were deliberately selected that do not contain content similar to that of the alcohol BI. To ensure parallel attention and number of contacts across groups [41], patients in Arms 2 and 3 also receive a 5–15 minute follow-up telephone call at 2 weeks post-discharge to inquire about general well-being and to review brochure content. Arms 2 and 3 serve as “usual care” insofar as alcohol screening or intervention for hazardous drinking is not routine standard of care for hospitalized patients at this VA medical center.

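### The control arms are not matched to BI on number of contacts as claimed, and the stated drinking feedback to both control arms is inconsistent with the aim of confining alcohol feedback to BI

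*Protocol article*

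**What the plan says.** **Contacts.** In the protocol article, under Arms 2 & 3: Control conditions, both control arms receive "healthy lifestyle brochures that address general healthy lifestyle behaviors such as dietary recommendations, tobacco cessation, and weight management". They also receive a 5–15 minute "follow-up telephone call at 2 weeks post-discharge to inquire about general well-being and to review brochure content". The reason given for the call is "To ensure parallel attention and number of contacts across groups".

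The BI arm has three parts, each put at about 15 minutes in Table 3: a core session, a second session and a telephone call at about 2 weeks. On the second, the Arm 1 section says "Part II consists of a single, brief, in-hospital or telephone follow-up session, with the same nurse interventionist", and Table 3 lists it as "Part II: In-hospital follow-up session (12–24 hours after core brief intervention, ~15 minutes". A Discussion heading confirms that the BI includes two follow-up sessions.

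**Alcohol feedback.** On the control materials, the article says "Brochures were deliberately selected that do not contain content similar to that of the alcohol BI". Under Assessment of intervention fidelity, program differentiation is defined as how far alcohol-related feedback and counseling reach the BI group alone, with contamination between conditions as the stated worry. Under Attention to potential AR, among the measures meant to reduce assessment reactivity, the article says "normative feedback about drinking behavior to both control group participants is provided within the context of general health maintenance recommendations".

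**The concern.** An attention control separates the content of an intervention from the time and contact that come with it. A reader who trusts the claim of parity will attribute a BI effect to its content. If BI has one more contact than the controls, some of the effect may be non-specific contact.

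The feedback statement matters for a different reason. The Background explains that results move toward the null when both groups receive some intervention, and the trial is built to deal with that. Planned drinking feedback to controls would bring in the same mechanism by another route. A null result, which the authors intend to use in the debate on hospital performance measures, would then be harder to read. The comparator would also no longer be plain usual care.

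**Working it through.** **1. Contacts and time.** No formula is needed beyond counting and adding. All inputs come from Table 3 and from the Arm 1 and Arms 2 & 3 sections.

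| Component | BI | AC and AC-LA |
|---|---|---|
| In hospital, first | Part I, about 15 min | Brochures, hand-over not timed |
| Second contact | Part II, about 15 min | None described |
| About 2 weeks | Part III, about 15 min | Call, 5–15 min |

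*Follow-up only* (Part I and the brochure hand-over both left out):
- Contacts: BI 2, controls 1.
- Minutes: BI 15 + 15 = 30; controls 5–15.
- Gap: 30 − 15 = 15 to 30 − 5 = 25 minutes.
- Ratio: 30/15 = 2 to 30/5 = 6.

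*All components:*
- Contacts: BI 3; controls 2 if the hand-over counts as a contact, otherwise 1.
- Minutes: BI 3 × 15 = 45; controls 5–15 plus an unstated hand-over time. The total gap cannot be computed. For it to be zero, the hand-over would have to last 45 − 15 = 30 to 45 − 5 = 40 minutes, and nothing in the article suggests that.

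The number of contacts is unequal on every count. The 2-week call corresponds to Part III. With the control call at its 15-minute maximum, the follow-up gap is 15 minutes, which is Part II. Assessment contacts are left out. In Table 2 they add nothing to the control arms that BI lacks.

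**2. Feedback to controls.** Three statements side by side:
- *Control conditions:* general lifestyle brochures and a call about well-being and the brochures. Drinking feedback is not mentioned. It is not forbidden either: the topic list is illustrative, and the exclusion concerns brochures with content like that of the BI.
- *Program differentiation:* the aim is alcohol-related feedback and counseling in BI only. The type of feedback is not limited.
- *Attention to potential AR:* normative feedback about drinking is provided to both control groups, in the present tense and without condition.

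The third statement cannot be squared with the aim in the second, and the first does not mention it. Feedback also belongs to the active content of BI. It is one of the FRAMES components, and Table 3 lists "Personalized feedback linking alcohol use and health" in the core session.

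**3. Would monitoring resolve it?** At 2 weeks and 6 months, all groups are asked to recall any *additional* alcohol feedback, recommendations or counseling, and the analysis plan categorizes its type, provider and context. This might capture feedback delivered by the study, but the word *additional* leaves that unclear.

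**The case against.** **On contacts.** The parity claim is attached to the 2-week call, and that call does match Part III. The claim concerns all contacts, so 3 versus 2 is arguably the fairer count than 2 versus 1. A condensed article may omit in-hospital contact with controls, and how closely to match attention is partly a design choice. What stands: the call is matched, and the 15–25 minute gap covers follow-up only. But the article itself asserts an equal number of contacts, and its own schedule shows otherwise on either count.

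**On feedback.** Normative feedback set within general health advice is not the personalized risk feedback, advice and change plan of the BI, and normative feedback is not a listed BI component. The article cites a source for this measure that cannot be examined here. What stands: the difference in intensity is real, and the feedback would not amount to giving controls the BI. But program differentiation is worded for alcohol-related feedback generally, and the monitoring questions count feedback even without counseling.

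**Stronger readings that a reader might infer, and that the article does not support:**
- *That program differentiation cannot be met.* It is defined as an extent to be measured, not as a threshold to pass. Feedback to controls works against its aim; it does not fail a test.
- *That the assessment-reactivity contrast is confounded.* The feedback goes to both control arms. A shared component does not by itself confound AC versus AC-LA, which differ in the extent of assessment, nor does it reverse the hypothesized ordering of the arms.
- *That the trial is biased in a known direction.* Extra contact may favour BI, and feedback to controls may work against it. The article gives no basis for weighing one against the other.

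**Conclusion.** The point holds in two limited parts.

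1. The claim of parallel attention and number of contacts is not delivered as described. Follow-up contacts are 2 versus 1, with about 15–25 minutes of follow-up unmatched; counting the hand-over, contacts are 3 versus 2. BI Part II has no described counterpart, so a BI effect may include non-specific contact. This rests on the stated session lengths and on the controls having no contact beyond those described.

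2. Stated drinking feedback to both control arms is inconsistent with the BI-only aim of program differentiation and is missing from the control description. If delivered, it may bias BI versus control toward the null. This assumes that such feedback has some effect on drinking.

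No figure for the effect on drinking or on power can be derived. Both parts concern what a result may be attributed to and what the comparator is called; neither invalidates the comparison. Severity is minor to should-fix, with moderate confidence.

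**What to change.** **Control conditions section.** Replace the parity claim with wording such as: *Attention is partly matched. The 2-week call corresponds to Part III of the BI; Part II has no counterpart in the control arms, so an effect of BI may include non-specific contact.*

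**Attention to potential AR section.** Do not give drinking feedback to controls, and delete the sentence. If it has already been given:
- describe it among the control components;
- record its delivery separately from the additional feedback that participants are asked to recall;
- limit program differentiation to BI-style feedback and counseling, such as the personalized feedback in Table 3;
- describe the comparator as usual care plus normative feedback, and state the possible dilution toward the null.

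**Cost.** Changes of wording in three sections and, only if feedback was given, one delivery-record item. No new contacts or staff are needed, and the sample size and analysis do not change. The control condition will read as slightly less strong than it does now.

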### Assessment of intervention fidelity

Assessment of intervention fidelity focuses on factors that impede delivery of the intervention and avoid interventionist drift. In our prior work, inpatient nurses identified numerous factors that could affect intervention fidelity and feasibility (e.g., time, potential interruptions for clinical care, and patient privacy and engagement) [49]. Features of acute care delivery and the inpatient setting, such as frequent need for clinical care/testing and shared patient rooms, may significantly impede BI delivery and compromise intervention integrity [50]. Only one other BI study among hospitalized patients has reported efforts to ensure intervention fidelity [12]. Other negative trials either explicitly report difficulties ensuring intervention fidelity (e.g., intervention duration, techniques) [14], or do not report on intervention fidelity at all [15,16].

### Limitation of the entire sample to hazardous, nondependent drinkers

Hazardous, nondependent drinkers are the population for whom BI was intended and in whom it has the greatest demonstrated efficacy [51,52]. Individuals with alcohol dependence typically require treatment of greater intensity and duration than BI provides, and particular attention to issues of loss of control, tolerance, and withdrawal. Other (null) trials of BI for hospitalized patients have included heavier-drinking and/or dependent individuals [12,14,19]. However, as noted earlier, in one case, when the sample was later restricted to hazardous, nondependent users, effects for reduced alcohol consumption were in fact detected [13]. We consider inclusion of only hazardous drinkers in the sample to be a strength because it eliminates the potential “noise” (and null effects) caused by including individuals in the sample for whom BI is not intended.

This study is not designed to answer questions of BI’s efficacy in other groups of drinkers (e.g., dependent individuals), where evidence for the efficacy of BI is uncertain [51,53]. Nonetheless, we recognize the fact that TJC measures do require BI for all patients with a positive alcohol screening (thus potentially requiring BI for patients who also meet criteria for alcohol dependence). Our study results will not be able to address the efficacy of BI for individuals with an alcohol use disorder.

### Patient-level randomization and unequal allocation of patients to groups in a 2:1:1 ratio

This aspect of study design allows more veterans to be exposed to the expected efficacious intervention and permits a more economically feasible study, because fewer hospital units will be needed than with cluster randomization. Also, each hospital unit has its own unique staff, administration, and culture that could influence the delivery and efficacy of the BI. With our design, unit characteristics are equally distributed across participants.

### A three-part BI discussion that includes two follow-up sessions

Follow-up sessions have been recommended by other researchers to increase the effect and salience of the BI [12,40] and to allow exploration of ways to integrate inpatient BI with ongoing attention to hazardous alcohol use in primary care, post-discharge.

### Additional considerations

As our overarching goal is to inform the debate about the efficacy of alcohol BI for hospitalized individuals in the context of imminent widespread adoption of TJC hospital performance measures, this study was not designed as an effectiveness trial that mirrors the measures’ current “real-life” specifications, particularly since such measures are subject to modification by TJC as well as VA’s own External Peer Review Program. Nonetheless, we recognize that our use of the NIAAA questions to determine study eligibility/need for a BI is slightly different from what is specified in the measures from TJC. Specifically, TJC measures dictate that individuals be screened using a validated screening instrument (such as the AUDIT-C) and that individuals with a positive alcohol screen must then receive a BI [4]. Additional assessment of alcohol consumption is not required to make the determination of need for a BI. In contrast, in the VA Substance Use Disorder Clinical Practice Guidelines, the need for BI is not determined by screening result, but by the results of “additional assessment” (i.e., determination of whether the patient is drinking above the NIAAA limits or drinking despite contraindications) [28].

We nonetheless anticipate that the applicability of our results from this trial will not be severely hampered by these differences in use of the NIAAA questions versus AUDIT-C to determine need for BI. If our study ultimately demonstrates the efficacy of BI for reducing drinking in hospitalized patients, then one could argue that we have generated evidence for the efficacy of BI in a “more severe” patient population of drinkers (i.e., those who exceed the NIAAA limits) and that its efficacy in a “less severe” group (i.e., those who “only” had a positive AUDIT-C screen) would still be in question. However, this assertion would be valid only if the AUDIT-C has a high rate of false negatives (i.e., patients who score negative on the AUDIT-C despite drinking above the NIAAA-specified limits). Importantly, in one recent study of almost 500,000 individuals, only about five percent of men and three percent of women in the study had negative AUDIT-C screens, despite reported heavy episodic drinking (i.e., drinking above daily limits) [54].

## Conclusion

The results of this trial will provide greater justification for or against the use of BI performance measures in the inpatient setting, as well as help inform organizational responses to BI-related hospital accreditation and performance measures from TJC and other entities interested in quality of care. Our intervention fidelity and execution data can also inform the specifications of such measures and their implementation. Administrators and clinicians charged with alcohol-related performance measurement and corresponding BI implementation will require efficacious, practical, and patient-centered BI delivery models.

## Abbreviations

AC: Attention control
AC-LA: Attention control - limited assessment
AR: Assessment reactivity
AUDIT-C: Alcohol use disorders identification test – consumption
BI: Brief intervention
CIDI-SAM: Composite international diagnostic interview, substance abuse module
DSM: Diagnostic and statistical manual of mental disorders
EMR: Electronic medical record
ES: Eligibility screening
FRAMES: Feedback, responsibility, advice to change, menu of options, empathy, self-efficacy
IRB: Institutional review board
MI: Motivational interviewing
MINT: Motivational interviewing network of trainers
NIAAA: National institute on alcohol abuse and alcoholism
OEF: Operation enduring freedom
OIF: Operation Iraqi freedom
PI: Principal investigator
RA: Research assistant
SIP-2R: Short inventory of problems – short version
SOCRATES: Stages of change readiness and treatment eagerness scale
TJC: The joint commission
VA: Veterans affairs
VAPHS: VA Pittsburgh healthcare system
